### 1.17.3 Secondary outcome measures

Secondary outcomes will be

- the incidence of acute kidney injury based on creatinine according to risk, injury, failure, loss, end-stage (RIFLE) classification in the first 3 days hours after surgery,
- the increase between baseline and peak chloride levels in the first 3 days after surgery
- the development of metabolic acidosis (defined as a base deficit > 2 mEq/L or a bicarbonate level <20 mmol/L) in the first 3 days after surgery
- the development of acidemia defined as a pH <7.3 in the first 3 days after surgery
- Postoperative complications
- Need for and duration of renal replacement therapy,
- Proportion of patients requiring mechanical ventilation
- Need for ICU admission
- ICU and hospital length of stay, and
- ICU and in-hospital mortality

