### 1.7 Study design

This study aims use an interventional design to provide high quality pilot data in a rapid time frame to address this important question and to help decide whether a pivotal randomized controlled trial is justified. Thus, all patients undergoing surgery at Austin Hospital will be randomly assigned to receive either Saline (0.9%) or the balanced crystalloid solution Plasmalyte as the primary crystalloid fluid in a blinded fashion during two study periods.

**The SPLIT Study: Saline (0.9%) vs. Plasma-Lyte® 148 Fluid Intervention Trial in Major Surgery Patients, Version 3, 1st Oct 2014**

The study will be conducted over a 4-month period allowing two interventional periods of 6 weeks each, with a three week wash-in and a three week wash-out period for each group. Blinded study fluid will be used for all crystalloid therapy in all participants. Austin Hospital staff specialists in anaesthesia agree that on the basis of current evidence, Saline (0.9%) and Plasmalyte are equally acceptable for crystalloid fluid therapy in every situation requiring major surgery with the exclusion of surgery for liver transplantation, renal transplantation and patients with raised intracranial pressure, where specific hospital perioperative fluid protocols are used in these settings.

Both Saline (0.9%) and Plasmalyte will be available for open-label administration in the rare situations, where, in the opinion of the treating anaesthetist or clinician, there is a clinical indication for one fluid or the other. This may occur, for example, in the setting of severe acidosis where the higher chloride content of saline may make this fluid problematic because it may increase the severity of such acidosis.

All adult patients who receive blinded or open-label fluid during one of the two-month study blocks will be analysed. The primary outcome will be the proportion of patients with kidney injury or failure based on established criteria. Secondary outcomes will include delta creatinine (the difference between baseline and peak creatinine), serum electrolyte levels, bicarbonate level, requirement for renal replacement therapy, complications and in-hospital mortality.

All of the data required for this study are collected routinely as part of standard clinical care and/or quality assurance activities.

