### 1.15 Baseline data

The following baseline data will be collected:

- Age
- Gender
- Admission type (elective vs. emergency)
- Type of surgery (hepatobiliary, colorectal, upper GI, orthopaedic etc.)
- If admitted to ICU: Chronic APACHE co-morbidities (including long-term dialysis)
- If admitted to ICU: APACHE-III admission diagnosis
- If admitted to ICU: Illness severity based on the on the APACHE-III risk of death score
- Baseline creatinine.
- Baseline biochemistry

**(Note: - all of these data are routinely collected for quality assurance purposes or as measured as part of usual clinical care)**

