### 1.30 Analysis plan

A complete description of the statistical analyses will be specified in a statistical analyses plan, finalised prior to completion of the study.

All analyses will be conducted on an intention-to-treat basis.

The primary analyses will be unadjusted analyses in which binary outcomes will be compared using relative risks with 95% confidence intervals and chi square tests and continuous outcomes will be compared with the use of mean

**The SPLIT Study: Saline (0.9%) vs. Plasma-Lyte® 148 Fluid Intervention  
Trial in Major Surgery Patients, Version 3, 1st Oct 2014**

differences and un-paired T-tests assuming that normality assumptions are met. If normality assumptions are not met then we plan to attempt simple data transformation, such as a logarithm transformation, and if this fails to proceed to a Mann-Whitney rank based test. Adjusted analyses will be performed using Poisson regression for binary outcomes and linear regression for continuous outcomes. Baseline covariates will include age, gender, elective vs. emergency surgery, surgical specialty of admission, type of operation, and baseline serum creatinine level. Survival times will be compared using log-rank tests and presented as Kaplan-Meier curves.

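### Rise in chloride is compared mainly as an unadjusted change score with a log-then-rank fallback, and baseline chloride is missing from the listed covariates of the adjusted model

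*Protocol*

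**What the plan says.** Section 1.17.3 lists as a secondary outcome "the increase between baseline and peak chloride levels in the first 3 days after surgery", which is peak minus baseline for each patient.

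Section 1.30, repeated in the synopsis, gives three rules that apply to it:

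- The main comparison is unadjusted: "The primary analyses will be unadjusted analyses in which binary outcomes will be compared using relative risks", and continuous outcomes by mean "differences and un-paired T-tests assuming that normality assumptions are met".
- If normality is not met, the plan is to try "simple data transformation, such as a logarithm transformation, and if this fails to proceed to a Mann-Whitney rank based test".
- A further set of models is planned alongside the unadjusted comparison: "Adjusted analyses will be performed using Poisson regression for binary outcomes and linear regression for continuous outcomes". The covariates are age, gender, urgency of surgery, specialty, type of operation and baseline serum creatinine. Baseline chloride is not among them.

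Section 1.15 collects "Baseline biochemistry". It does not name chloride, but the outcome itself requires a baseline chloride value.

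For creatinine, a change outcome appears only in section 1.7, as "delta creatinine (the difference between baseline and peak creatinine"). Section 1.17.3 covers creatinine only through RIFLE incidence.

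**The concern.** Two features suit the chloride outcome badly.

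First, the fallback. Peak minus baseline can be zero or negative, and a logarithm is then undefined. Table 1 makes this plausible: Plasmalyte has chloride 98 meq/L against a plasma median of 102, and saline has 150. Non-positive changes would be expected more often under Plasmalyte, so dropping or shifting those values could distort the comparison. The next step, Mann-Whitney, answers a different question and gives no difference in mmol/L. The choice between the steps would be made after seeing the data.

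Second, the baseline. A change score fixes the coefficient of baseline at 1, whereas regression estimates it. As listed, neither the unadjusted nor the adjusted analysis estimates it for chloride, so both give up precision that a value already in hand would supply. Chloride load is the mechanism that the background puts forward for kidney injury, so its effect estimate should be as sharp and as readable as the data allow.

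**Working it through.** **Inputs.** About 1000 patients per group (section 1.10). The protocol gives no SD, correlation, target difference or power for chloride, so there is no stated figure to reproduce for this outcome. Its one power statement, in section 1.29, concerns RIFLE injury or failure (14% against 8.4%, alpha 0.01, more than 80% power). With 1000 per group it recomputes to 91.9% two-sided, so it stands and does not bear on this point.

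**Precision.** Let baseline and peak have the same SD (assumed) and correlation r (assumed).

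- Variance of the change score is proportional to 2(1−r).
- Variance of the baseline-adjusted comparison is proportional to 1−r².
- Ratio, adjusted to change: (1−r²)/[2(1−r)] = (1+r)/2.

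| assumed r | variance ratio | extra patients the change score needs | 2000 patients by change score are worth |
|---|---|---|---|
| 0.3 | 0.65 | 54% | 1300 |
| 0.5 | 0.75 | 33% | 1500 |
| 0.7 | 0.85 | 18% | 1700 |
| 0.9 | 0.95 | 5% | 1900 |

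The third column is 1/ratio − 1 and the fourth is 2000 × ratio. A simulation with 1000 per arm gave ratios of 0.62, 0.75 and 0.85 at r = 0.3, 0.5 and 0.7.

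**Absolute scale.** Assume SD 2.5 mmol/L (a quarter of the 98 to 108 range in Table 1) to 4 mmol/L. At SD 4 and r = 0.3, the SE of the change-score difference is 4 × √(1.4 × 2/1000) = 0.21 mmol/L. With baseline adjustment it is 4 × √(0.91 × 2/1000) = 0.17. These assume that all 1000 per group have both values.

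**Baseline differences between blocks.** Each fluid has one 6-week block (section 1.17). Let τ be the true fluid effect on peak chloride.

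- Difference d that regresses to a common mean: the peak difference is τ + r·d. The change score gives τ − (1−r)d and adjustment gives τ. Simulated slopes on d at r = 0.3, 0.5 and 0.7 were −0.73, −0.51 and −0.32 for the change score, and between −0.03 and −0.01 with adjustment.
- Stable shift s at both baseline and peak, such as assay drift between blocks: the peak difference is τ + s. The change score gives τ and adjustment gives τ + (1−r)s.

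The sign of the argument therefore depends on the kind of imbalance, and the protocol does not settle which kind to expect.

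**Creatinine.** Regressing the change on fluid and its own baseline gives the same fluid coefficient as regressing the peak on them. The adjusted model lists baseline creatinine, so it already achieves this.

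**The case against.** The case for leaving the plan alone has several sound parts.

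- **The effect size would be reported anyway.** A reader might infer that the chloride effect disappears if the rank test is triggered. It does not: the adjusted linear regression for continuous outcomes is planned as well and gives a difference in mmol/L. What stands is that the main result could then be on a different scale from the adjusted one.
- **Bias.** A reader might infer that the change score is biased by a sizeable block imbalance, say 1 mmol/L, and that adjustment cures it. No such imbalance is documented. With SD 2.5 to 4, the SE of the baseline difference is SD × √(2/1000) = 0.11 to 0.18, so 1 mmol/L is about 6 to 9 SE and could not be chance. It would need a systematic period shift, and if that shift were stable, adjustment would be the worse of the two estimators. The bias argument is not general.
- **Benchmark.** The 1.7 mmol/L in the liver resection trial is Plasmalyte against Hartmann's. The saline-Plasmalyte figure in the protocol is 5.4 mmol/L, in healthy volunteers. Against that, even the largest SE above (0.21) is small, so detecting a chloride difference is not in doubt. The gain is a narrower interval.
- **Creatinine.** A reader might extend the criticism to creatinine in full. The adjusted model already contains its baseline; only the choice of main analysis is open.
- **The logarithm is only an example,** and a transformation that fails passes on to the next step. True, but the next step is the rank test, and with about 1000 per group a comparison of means does not need normal data.
- **Detail belongs to the statistical analysis plan.** The full description is deferred to it, and the covariate list may not be exhaustive. But section 1.30 itself fixes the unadjusted main analysis and the fallback sequence.

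**Conclusion.** The point holds for chloride, and it is modest. The listed analyses do not use baseline chloride as a covariate, and the fallback sequence does not fit an outcome that can be zero or negative. Using the baseline would cut the variance to between 0.65 and 0.95 of its change-score value for r from 0.3 to 0.9, given equal SDs. The true r is unknown, and at the top of that range the gain is small. The protocol does not support a claim of bias in a known direction, nor one of an unreported effect. Only secondary outcomes are concerned.

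**What to change.** In section 1.30, for the chloride outcome:

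- Make the main analysis a linear regression of peak chloride (or its change; the fluid coefficient is the same) on fluid, baseline chloride and the covariates already listed, with heteroscedasticity-robust standard errors.
- Report the adjusted mean difference in mmol/L with its 95% confidence interval.
- Remove the transformation and rank-test sequence for this outcome.
- Keep the unadjusted difference in change as a sensitivity analysis. With one block per fluid, baseline adjustment does not cure a systematic period shift, and a gap between the two results would be a warning of one.

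For the creatinine change, if it is retained as an outcome, name the planned model with baseline creatinine as the main analysis.

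The cost is wording. No new data are needed, and a patient without a baseline chloride has no change score under the present plan either.

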## ETHICS

### 1.18 Guiding principles

This study is to be performed in accordance with World Medical Association Declaration of Helsinki: Ethical principles for medical research involving human subjects (WMA 2008), the International Ethical Guidelines for Biomedical Research Involving Human Subjects (CIOMS 2002) and the National Statement on Good Practice in Human Research

The research utilises information normally gathered during the course of the delivery of a currently recognised treatment and will maintain anonymity and privacy and can therefore be conducted in accordance with Australian Law and the National Statement.

**As a result of these factors, this study involves negligible risk.**

The study design will provide high quality information about an important clinical question from a very large number of subjects in a short period of time. Given the low risk nature of the research, we will use a process of '**opt-out consent**' that involves the provision of information to patients and their next of kin and the opportunity to opt-out from the use of their data if they wish.

## **1.20 Confidentiality of patient data**

Patients will be allocated a unique study number. Study data will be obtained from routinely collected quality assurance and clinical information. Data entered into the study database will be identified by the unique study number only. The enrolment log and the study data will be kept separately.

## DATA MANAGEMENT

### 1.21 Data collection methods

The demographic, biochemical, and outcome data used in this study are already collected by the Austin Hospital for administrative and quality assurance purposes.

Any ICU data are similarly collected and already provided to the Australian and New Zealand Intensive Care Society Centre for Outcome and Resource Evaluation as part of a government-funded bi-national quality assurance programme.

The only data used in this study which are not routinely collected for quality assurance purposes are the daily volume of study fluid administered as fluid boluses and the data relating to renal outcomes. These data will be collected by the Principle investigators or trained Research Co-ordinators.

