Large scale fluid trials using conventional randomised controlled trials are feasible; however, they are extremely expensive and time-consuming to conduct and can only be justified if initial work in the population of interest (major surgery patients) provides preliminary evidence of a possible effect. The recently completed CHEST study comparing saline (0.9%) to the colloid hydroxyethyl starch for fluid resuscitation in intensive care trial in which the Austin Hospital was involved randomised 7000 patients and took 10 years to from inception to publication and cost approximately \$5 million dollars to complete.

This proposal outlines a research approach that has the potential to provide key preliminary information and data for logistic feasibility, amounts of fluids used, safety data on the incidence of adverse events and preliminary outcome data for power calculations. Such information is crucial to the design of a subsequent pivotal trial.

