## OBJECTIVES

The overall objective of this study is to establish the feasibility, safety and relative biochemical and physiological efficacy of using saline (0.9%) vs. Plasmalyte solution as the primary fluids in adult major surgery patients.

The choice of non-crystalloid fluid intervention such as colloids, or any other blood product e.g. red blood cells, platelets, cryoprecipitate, frozen plasma, bicarbonate, dextrose etc. will be entirely at the discretion of the all clinicians caring for the patients

Specifically, we aim to establish the effect of saline (0.9%) and Plasmalyte solution on:

1. The development of acute kidney injury in hospital
2. The development of biochemical and acid-base derangements
3. The development of postoperative complications
4. Requirements for renal replacement therapy
5. Requirements for mechanical ventilation
6. Hospital length of stay
7. Hospital mortality

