## STUDY DESIGN

### 1.12 General

This study is a single-centre pilot prospective pilot study comparing saline (0.9%) and Plasmalyte solution for all perioperative crystalloid fluid therapy in adult major surgery patients.

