### 1.16 Study treatments

This study is designed to compare two approaches to fluid therapy. It will compare use of Saline (0.9%) or Plasmalyte as the primary default crystalloid fluids.

Blinded study fluid will be provided by Baxter Pty in indistinguishable 1000ml bags. Open label fluids will be available for use in rare situations where the treating clinician believes that there is an indication for one fluid or the other. This may occur, for example, in the setting of severe acidosis where the higher chloride content of saline may make this fluid undesirable because it may increase the risk of more severe acidosis.

**The SPLIT Study: Saline (0.9%) vs. Plasma-Lyte® 148 Fluid Intervention Trial in Major Surgery Patients, Version 3, 1st Oct 2014**

Anaesthetists and surgeons, and intensivists, as well as all clinicians at Austin Hospital have indicated that they regard the study fluids as equally acceptable in essentially every clinical setting in which crystalloid fluid therapy is required. Irrespective of which study fluid the patient receives they will be analysed on an intention to treat basis.

The overall volume of study fluid and any open label study fluid administered as fluid boluses will be recorded daily.

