### **1.17 Treatment allocation**

Patients will be randomly assigned, in alternating 6 weeks blocks to use either blinded Saline (0.9%) or Plasmalyte solution. There will be a three week wash-in period and a three-week wash-out period between each fluid intervention.

For example, assume:

**GROUP ONE:** Saline (Blinded)

**GROUP TWO:** Plasmalyte (Blinded)

Three weeks prior to commencement, blinded Saline will be introduced into all theatres, ICU and surgical wards for a 3 week wash-in period. **GROUP ONE** subjects will then receive Saline (blinded) for 6 weeks. This will be followed by a 3-week wash-out period of Saline (blinded). Plasmalyte solution (blinded) will then be washed-in for 3 weeks. **GROUP TWO** subjects will then receive Plasmalyte solution (blinded) for a 6 week period. Plasmalyte solution (blinded) will be washed-out for 3 weeks and the study will stop.

Total study duration: 24 weeks

Any patients who remain in hospital throughout the transition period will continue to receive the blinded fluid that they were originally assigned to for all postoperative crystalloid intervention. Thus blinded fluid will be made available as the only crystalloid fluid in all surgical wards and in the intensive care unit. No controls will be placed on the use of colloidal fluid therapy, blood products (red blood cells, platelets, cryoprecipitate or fresh frozen plasma, or any other fluid non-crystalloid fluid intervention e.g. dextrose, bicarbonate.

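### Sections 1.16 and 1.21 disagree on which fluid volumes are recorded, and neither clearly captures all the trial crystalloid given

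*Protocol*

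**What the plan says.** The intervention covers all crystalloid. Section 1.7 states: "Blinded study fluid will be used for all crystalloid therapy in all participants". Section 1.12 describes a study "comparing saline (0.9%) and Plasmalyte solution for all perioperative crystalloid fluid therapy in adult major surgery patients", and section 1.17 adds: "Thus blinded fluid will be made available as the only crystalloid fluid in all surgical wards and in the intensive care unit". Sections 1.7 and 1.16 allow open-label saline or Plasmalyte in rare situations, with severe acidosis as the example.

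The Background and Rationale says the pilot can provide "key preliminary information and data for logistic feasibility, amounts of fluids used, safety data on the incidence of adverse events", and calls such information crucial to designing the later trial. Feasibility heads the aims: "The overall objective of this study is to establish the feasibility, safety and relative biochemical and physiological efficacy".

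Two sections say what volume is recorded:

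- Section 1.16: "The overall volume of study fluid and any open label study fluid administered as fluid boluses will be recorded daily".
- Section 1.21: the only items not routinely collected for quality assurance "are the daily volume of study fluid administered as fluid boluses and the data relating to renal outcomes". It describes the routine data as demographic, biochemical and outcome data, plus ICU registry data, and does not mention fluid volume.

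Fluid volume is not in the baseline data (1.15), the primary outcome (1.17.2) or the secondary outcomes (1.17.3).

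**The concern.** Boluses are only part of perioperative crystalloid. Intraoperative and maintenance infusions are also part of the assigned treatment. A data collector working from 1.21 would abstract boluses and stop there. One working from 1.16 might abstract all blinded fluid but only the bolus part of open-label fluid. The protocol does not say which is meant.

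What is at stake is the description of exposure: how much trial fluid each arm received, and how much of it was not the allocated fluid. A pivotal trial would take both from this pilot. This cannot be left to a statistical analysis plan, because volumes that were never abstracted cannot be analysed.

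**Working it through.** The protocol states no figure to reproduce. The check is a comparison of the texts, followed by arithmetic on assumed shares.

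**The readings side by side**

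| Reading | Blinded fluid recorded | Open-label fluid recorded | What is lost |
|---|---|---|---|
| Narrow: 1.21, or 1.16 with the bolus qualifier applied to both fluids | Boluses only | Boluses only, if recorded at all (1.21 does not name it) | Intraoperative and maintenance volume |
| Wide: 1.16 with the qualifier applied to open-label fluid only | All | Boluses only | Open-label infusions |

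The wide reading contradicts 1.21. The narrow reading fits 1.21 but falls short of the all-crystalloid intervention and of the promised data on amounts used. No other section requires infusion volumes to be abstracted.

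**Illustrative size**

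Inputs:

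- Volume per patient: 10 L, the budgeting figure in section 1.34. It is not a measured volume.
- Bolus share *b*: not given; assumed 10 to 50%.
- True open-label share of volume *s*: not given; assumed 5 and 10%.

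Narrow reading, recorded litres per patient = 10 × *b*:

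- *b* = 0.10: 10 × 0.10 = 1.0 L
- *b* = 0.25: 10 × 0.25 = 2.5 L
- *b* = 0.50: 10 × 0.50 = 5.0 L

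Wide reading, with blinded fluid counted in full and open-label fluid only as boluses: recorded open-label share = *sb* / (*sb* + 1 − *s*).

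- *s* = 0.05, *b* = 0.10: 0.005 / 0.955 = 0.52%
- *s* = 0.05, *b* = 0.50: 0.025 / 0.975 = 2.56%
- *s* = 0.10, *b* = 0.10: 0.010 / 0.910 = 1.10%
- *s* = 0.10, *b* = 0.50: 0.050 / 0.950 = 5.26%

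Narrow reading, crossover share, if boluses of both fluids are recorded and *b* is the same for each: *sb* / (*sb* + (1 − *s*)*b*) = *s*. The share is then not understated; only the litres are. So the lost total and the understated crossover arise under different readings and cannot be added together.

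**The case against.** The strongest reply is that 1.21 does not set a recording rule. Its sentence sorts data by source, listing what lies outside quality assurance collection. The operative instruction is in 1.16, where the reference to overall volume most naturally means the total, and the bolus qualifier stands next to the open-label fluid. Sections 1.7 and 1.20 also name clinical information as a data source, so infusion volumes may be in the charts. Much of this stands: a reader should not infer that the protocol definitely limits recording to boluses. It does not remove the disagreement. Section 1.21 does not list fluid volume among the routine data, it singles out bolus volume for the investigators or research coordinators to collect, and nothing requires infusions to be taken from the charts.

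Second, on the wide reading the gap is small, because open-label use is expected to be rare. That is fair. Still, the amount of open-label use is itself something a pilot should measure, and the example of severe acidosis suggests it could differ between arms.

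Third, litres supplied per period divided by patients treated could check the 10 L assumption without bedside records. That would be a rough check. The protocol plans no such count, wash-in, wash-out and non-trial use would blur it, and it would give nothing per patient.

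Fourth, the secondary outcomes, such as "the increase between baseline and peak chloride levels in the first 3 days after surgery", show whether the arms separated biochemically. They do, but indirectly and not in litres.

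A reader might also infer that the kidney injury comparison is compromised, or that the 10 L figure's weight in the budget measures the loss. Neither follows. Volume enters no listed outcome or planned test, and the budget describes fluid supply, not missing data.

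**Conclusion.** The point holds as an inconsistency between two recording instructions, neither of which clearly captures all the trial fluid. Under 1.21 as worded, intraoperative and maintenance infusions go unrecorded. Under the wider and more natural reading of 1.16, total blinded volume is available and only open-label infusions are missed, so crossover is understated. One harm or the other applies, not both.

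The text fixes the direction of each harm but not its size. The ranges in the working rest on an assumed bolus share of 10 to 50%, assumed open-label shares of 5 and 10%, and a budgeting figure for volume. They are illustrations, not estimates.

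The primary analysis, the intention-to-treat principle and the stated power are untouched. What suffers is a pilot deliverable promised in the background and the description of exposure and adherence. This is a cheap improvement worth making, not a threat to the main comparison.

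**What to change.** Delete the bolus qualifier from sections 1.16 and 1.21, and use the same statement in both: the total daily volume (bolus, intraoperative and maintenance) of blinded study fluid, of open-label saline and of open-label Plasmalyte is recorded for every patient. Report these volumes per arm as a feasibility result.

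The cost is some extra chart abstraction by staff who already collect daily volumes under 1.21, and a volume item on the case report form that separates the three products. Randomisation, fluid supply, outcomes and the primary analysis do not change.
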